
#### Study Intervention

TAU pregnant women in this condition will receive care as usual, which involves continued enrollment in OAT and continued obstetric care. We will also provide them with a printed handout containing information on NAS and local resources. This level of information meets or exceeds what most mothers in this situation usually receive. Participants in the TAU condition will not receive iPads with accompanying modules; however, the handout constitutes more information than they normally receive.

#### Adapted NAS Tool Intervention

Pregnant women in this condition will receive the adapted mobile-based NAS instructional tool and TAU. Women in this condition will go through the NAS instructional tool at least once during pregnancy, with their choice of going through the modules gradually while waiting at the OAT clinic to receive their dose or by scheduling a time to review the modules. Participants will have free web access to the tool throughout their third trimester and through 12 weeks postpartum so they can access the modules at any time and as many times as desired, including after giving birth. Women will be randomized 1:1 to the intervention or TAU conditions.

#### Data Collection and Outcomes

Although the primary outcomes of focus will be maternal drug relapse (assessed via Addiction Severity Index-Lite) and OAT continuation (“Are you currently receiving OAT (Yes or No)? Please explain*.*”), because of the exploratory nature of this trial, several other outcomes of interest will also be assessed. At the 3 follow-up appointments, participants will complete several measures assessing numerous maternal-newborn outcomes: the 9-item Patient Health Questionnaire, a psychometrically validated 9-item measure used to assess depression in a variety of populations [45-47]; the *Birth Satisfaction Scale-Revised*, a 10-item, Likert-type, birth satisfaction questionnaire that measures experiences of childbearing, stress, quality of care, and women’s attributes and that was psychometrically validated in the United States by our research team [42-44]; the *Parenting Stress Index short form*, which measures parental stress associated with the perception of having a difficult child or a dysfunctional parent-child relationship and consists of 36 items [48]; and the *Maternal Postpartum Attachment Scale (MPAS)* [40,41], which measures maternal-newborn bonding. The *MPAS* consists of 19 items assessing 3 dimensions: *pleasure in interaction with the infant* (5 items), *absence of hostility toward the infant* (5 items), and *quality of mother-infant attachment* (9 items), with higher scores indicating higher maternal postpartum attachment to the baby [37,40,41]. We will also collect other outcome measures, including the length of newborn hospital stay (“How many days did your newborn stay in the hospital”), newborn hospital readmission (“Has your newborn been readmitted to the hospital for any reason after discharge? If yes, how many times? Please list reasons for each readmission.”), and breastfeeding (“Are you currently breastfeeding? If yes, ‘How often do you breastfeed your baby?’ if no, ‘How long did you breastfeed your baby?’”). Acceptability and satisfaction of the NAS tool will also be examined at follow-up by the CSQ-8 to rate overall satisfaction with the adapted NAS tool [29]. Finally, participants will also complete the *10-item SUS* [30,31] (Table 2). Throughout their third trimester and postpartum, we will also send participants a brief weekly web survey link asking about the previous week’s frequency of use of the adapted mobile NAS tool and which specific modules participants viewed the most, if any, to track weekly frequency of use and preference of modules.

#### Data Analysis

Means (SDs) will be calculated for continuous variables, and percentages will be calculated for categorical variables for the 2 groups (intervention group and TAU group) at each assessment. Demographic and baseline characteristics will be tested across intervention versus TAU via independent-samples *t* tests and one-way analysis of variance (for continuous variables) and chi-square tests (for categorical variables). Generalized estimating equations will be used to analyze the primary longitudinal outcomes of maternal drug relapse and OAT continuation and secondary outcomes and to control for any baseline demographic differences across groups, where intervention versus TAU remains as the primary independent variable. Analyses will control for baseline and demographic outcomes and time. All inferential results will be presented as odds ratios with 95% CIs for binary outcomes and unstandardized regression coefficients with 95% CIs for continuous outcomes. We will use an α error rate of .05 as the threshold for statistical significance. All analyses will be conducted using STATA version 14.2.

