**Outcome measures**			
	Addiction Severity Index-Lite	✓	✓
	Maternal Postpartum Attachment Scale	N/A	✓
	Birth Satisfaction Scale-Revised	N/A	✓
	Patient Health Questionnaire-9	N/A	✓
	Parenting Stress Index	N/A	✓
	Client Satisfaction Questionnaire-8	N/A	✓
	System Usability Scale	N/A	✓
	Length of hospital stay for newborn	N/A	✓
	Newborn hospital readmission	N/A	✓
	Breastfeeding initiation and duration	N/A	✓
	Maternal OAT continuation and relapse	N/A	✓
	Frequency of NAS^d^ tool use (weekly)	✓	✓

^a^Data collected.

^b^N/A: not applicable.

^c^OAT: opioid agonist therapy.

^d^NAS: neonatal abstinence syndrome.

**Table 2 table2:** Outcomes and description of measures.

Study stage and outcome			Study design		Description of measures

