**Stage 3:** **Clinical trial comparing NAS tool with usual care**					
	Demographic characteristics	Randomized clinical trial		Demographics and baseline characteristics, such as age, education, marital status, time in the OAT^d^ program, number and age of living children, employment, and ASI-Lite^e^, will be collected at the start of the study to describe the sample and to serve as control variables when comparing groups on the outcomes.	
	Maternal drug use and relapse	Randomized clinical trial		Maternal drug use and relapse will be assessed via ASI-Lite, a standardized semistructured clinical interview that offers clinical information and assesses severity profiles in the following domains: medical, employment, alcohol, drug, psychological, legal, and family and social [34]. It has been shown to have adequate to good internal consistency, good test-retest reliability, independence across the domain composite scores, and agreement with the longer version of the ASI-Lite [34].	
	OAT continuation	Randomized clinical trial		OAT continuation will be assessed via a single question (“Are you currently receiving OAT (Yes or No)? Please explain”).	
	Length of newborn hospital stay and readmission	Randomized clinical trial		These will be determined by single questions: length of newborn hospital stay (“how many days did your newborn stay in the hospital”) and newborn hospital readmission (“has your newborn been readmitted to the hospital for any reason after discharge? If yes, how many times? Please list reasons for each readmission”).	

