	Maternal stress	Randomized clinical trial		PSI^h^ measures parental stress associated with the perception of having a difficult child or a dysfunctional parent-child relationship and consists of 36 items that are rated on a 5-point Likert scale (from 1=strongly agree to 5=strongly disagree), with higher scores indicative of less total stress [48]. PSI has been shown to possess good psychometric properties and has been validated in numerous samples, including high-risk families [49]. It includes parental distress, parent-child dysfunctional interaction, and difficult child subscales, all of which will be considered individually. The child and parent domains can and will be combined to form a total stress scale score.	
	Breastfeeding	Randomized clinical trial		Assessed via several questions “Are you currently breastfeeding? If yes, ‘How often do you breastfeed your baby?’, if no, ‘How long did you breastfeed your baby.’”	
	Frequency of NAS tool use	Randomized clinical trial		Throughout their third trimester and postpartum, we will also send participants a brief weekly web-based survey link asking about the previous week’s frequency of use of the adapted mobile NAS tool and which specific modules participants viewed most, if any, to track weekly frequency of use and preference of modules.	

^a^NAS: neonatal abstinence syndrome.

^b^SUS: Systems Usability Scale.

^c^CSQ-8: 8-item Client Satisfaction Questionnaire.

^d^OAT: opioid agonist therapy.

^e^ASI-Lite: Addiction Severity Index-Lite.

^f^MPAS: Maternal Postpartum Attachment Scale.

^g^PHQ-9: 9-item Patient Health Questionnaire

^h^PSI: Parenting Stress Index short form.

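### The time-adjusted GEE is assigned to every secondary outcome, but its two effect measures cannot handle right-censored breastfeeding duration, and length of stay, breastfeeding initiation and readmission are not repeated measures

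*Protocol article*

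**What the plan says.** The Stage 3 Data Analysis section names one inferential method. GEE "will be used to analyze the primary longitudinal outcomes of maternal drug relapse and OAT continuation and secondary outcomes". It adds: "Analyses will control for baseline and demographic outcomes and time". All inferential results are to be given as "odds ratios with 95% CIs for binary outcomes and unstandardized regression coefficients with 95% CIs for continuous outcomes", and "We will use an α error rate of .05 as the threshold for statistical significance".

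The secondary outcomes listed in the Methods Overview include length of newborn stay, readmission, and breastfeeding initiation and duration. Table 1 ticks "Length of hospital stay for newborn", readmission and breastfeeding in the single column that covers 4, 8 and 12 weeks postpartum.

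Table 2 and the Stage 3 Data Collection and Outcomes section give the items:

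- **Length of stay:** one question on the number of days in hospital.
- **Readmission:** "has your newborn been readmitted to the hospital for any reason after discharge", followed by how many times and why.
- **Breastfeeding:** whether the woman is breastfeeding now; if so, how often; if not, "How long did you breastfeed your baby".

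**The concern.** A GEE with time as a covariate suits an outcome measured afresh at each visit. Four of the named outcomes are not of that kind.

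- **Breastfeeding duration** is a time to stopping. A woman still breastfeeding at a visit has no duration yet; all that is known is that it exceeds the time since birth. The only measure the section offers for such a quantity is "unstandardized regression coefficients with 95% CIs for continuous outcomes", which has no place for a censored value.
- **Length of stay** is one number per infant, fixed at discharge.
- **Breastfeeding initiation** is one yes or no per woman.
- **Readmission** is asked as ever since discharge. Once the answer is yes it stays yes, so an early event counts at three visits and a late one at a single visit.

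The trial is meant to supply efficacy data for planning a fully powered trial. If the tool prolongs breastfeeding, the arm that benefits has more women with no duration to report, and the estimate handed to the next trial is too small. For the one-off and cumulative outcomes the risk is a standard error that treats one fact, reported three times, as three facts.

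**Working it through.** **Inputs from the article.** 30 women randomized 1:1, so 15 per arm; follow-up at 4, 8 and 12 weeks; α = 0.05, taken as two-sided because 95% CIs are reported. The article gives no event rates, SDs, durations or power, so there is no stated figure to reproduce and every distribution below is an assumption.

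**1. Breastfeeding duration.** Assume exponential durations with mean m. At week v:

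- Restricted mean (censoring handled): m(1 − e^(−v/m))
- Mean among women who have stopped: m − v·e^(−v/m)/(1 − e^(−v/m))
- Still breastfeeding: e^(−v/m)

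Worked example, m = 6 v 10 weeks, v = 12:

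- Restricted means: 6(1 − 0.135) = 5.19 and 10(1 − 0.301) = 6.99; gap 1.80.
- Stoppers: 6 − 12(0.135/0.865) = 4.12 and 10 − 12(0.301/0.699) = 4.83; gap 0.71.
- Durations cut at each visit and pooled: the gaps at 4, 8 and 12 weeks are 0.38, 1.09 and 1.80; average 1.09.

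| Assumed mean duration (weeks) | Still breastfeeding at 12 weeks | 12-week restricted mean gap | Cut at each visit, pooled | Stoppers by week 12 only |
|---|---|---|---|---|
| 6 v 10 | 14% v 30% | 1.80 | 1.09 | 0.71 |
| 8 v 16 | 22% v 47% | 2.23 | 1.29 | 0.70 |
| 12 v 20 | 37% v 55% | 1.44 | 0.81 | 0.39 |
| 8.66 v 17.31 (medians 6 v 12) | 25% v 50% | 2.16 | 1.24 | 0.66 |

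The stopper-only gap is about 27% to 39% of the restricted-mean gap (0.39/1.44 = 0.27; 0.71/1.80 = 0.39). The pooled cut gap is about 56% to 61% (0.81/1.44 = 0.56; 1.09/1.80 = 0.61). This is a bias in the estimate, so the type of standard error does not affect it.

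**2. Length of stay, if entered at all three visits.** Three identical values per woman, treated as independent, shrink the SE by √3, so the large-sample type I error is 2(1 − Φ(1.96/√3)) = 2(1 − Φ(1.13)) = 25.8%. Simulation with 15 per arm, log-normal stays (log-SD 0.6), no true effect and visit in the model:

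| Analysis | Mean SE (days) | Type I error |
|---|---|---|
| One value per infant, t test | 3.37 | 4.1% |
| Three rows, independence, model-based SE | 1.92 | 28% |
| Three rows, independence, robust SE | 3.26 | 6.0% |
| Three rows, exchangeable | fit failed in 446 of 500 runs | SE near 0 in the rest |

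The mean model-based SE agrees with 3.37/√3 = 1.95. The exchangeable fit breaks down because the within-woman correlation is 1 and the matrix is singular.

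**3. Readmission, cumulative, if entered at all three visits.** With no effect and an assumed hazard of 0.04 per week, type I error was 20% with model-based independence SE and 4.0% with robust SE. With an assumed control hazard of 0.02 per week and a true hazard ratio of 0.5, the odds ratios at 4, 8 and 12 weeks were 0.49, 0.48 and 0.47, and the pooled value was 0.48. With 0.03 per week and a hazard ratio of 0.4, they were 0.39, 0.37 and 0.36, pooled 0.37. Pooling did not materially shrink the effect.

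**The case against.** The strongest defence is that three rows per woman is inferred. Table 1 has one follow-up column, and a tick there shows that an item belongs to follow-up, not that a one-off answer enters the model three times. The Data Analysis section attaches the word longitudinal to the primary outcomes, and a GEE with one record per woman is an ordinary regression. Row structure, working correlation and type of SE belong in a full analysis plan that is not shown, so their absence from the article is no fault. All of this stands, and it makes the false precision in length of stay and readmission conditional.

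A reader might go further and infer that all these outcomes will get wrong standard errors or effects shrunk towards zero. The document does not support that. Robust SEs, commonly paired with GEE, kept the type I error at 6.0% and 4.0%. The exchangeable fit on identical repeats mostly fails visibly. Pooled readmission was not materially shrunk under constant hazards.

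It can also be said that the article nowhere proposes a stoppers-only analysis, and that the current-breastfeeding item is a proper repeated binary outcome. Both are true. Women still breastfeeding at week 12 do supply information, namely a duration of at least 12 weeks. But duration is itself a named outcome, the section exempts no secondary outcome, and neither permitted effect measure can use that information as a censored time. The two ways of forcing duration into a linear coefficient that were checked both shrink the difference. That part of the concern survives.

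**Conclusion.** The point holds in a limited form. The sentence on GEE covers outcomes that are not repeated measures, and its two effect measures do not fit a right-censored duration. For breastfeeding duration the cost is a real difference of 1.4 to 2.2 weeks (restricted to 12 weeks) reported as 0.4 to 0.7 weeks among stoppers, or 0.8 to 1.3 weeks if cut at each visit and pooled. These sizes rest on exponential durations with assumed means; the direction was the same in all four scenarios.

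For length of stay and readmission the harm is conditional: a type I error of about 20% to 28% if they enter at three visits with model-based independence SE, and near nominal with robust SE. For readmission the remaining weakness is that a pooled odds ratio does not refer to readmission by any stated time.

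Severity is moderate. These are secondary outcomes in a 30-woman trial that calls itself exploratory, and the analysis of relapse and OAT continuation is unaffected.

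**What to change.** Exempt these outcomes from the repeated-measures GEE sentence and state:

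- **Length of stay and breastfeeding initiation:** one record per mother-infant pair. A rank-based comparison for length of stay is an option, not a requirement.
- **Readmission:** any readmission by 12 weeks, one row per infant, taken from the existing cumulative question at the last visit. Limiting the later surveys to the time since the previous one is optional.
- **Breastfeeding duration:** Kaplan-Meier or restricted mean to 12 weeks, with women still breastfeeding censored at their last visit. Add this effect measure to the list of reported results.
- **Breastfeeding status at each visit:** keep in the GEE with an odds ratio.

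The cost is a few lines of analysis wording. The existing questions already collect the data needed. The article puts the randomized stage in late 2022, after Stages 1 and 2, so on its own timeline the wording can be settled before outcome data exist.

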## Results

This project was funded in July 2020 (see Multimedia Appendix 1 for grant review summary statement) and approved by the institutional review board in April 2020. Data collection for stage 1 began in December 2020, and as of January 2021, we completed 18 semistructured interviews (10 with NAS providers and 8 with perinatal women receiving OAT). Common themes from all interviews will be analyzed in spring 2021 to inform the adaptation of the NAS caregiving tool. Results from stage 1 are expected to be published in summer 2021. Stage 2 data collection will commence in fall 2021, followed by the randomized controlled trial in stage 3 in late 2022.

## Discussion

### Conclusions

This study is highly innovative in several ways. First, despite the need to educate pregnant women at risk for delivering NAS-affected newborns and equip them with the skills necessary to successfully care for a newborn with NAS when they are pregnant, no published evidence-based interventions exist to prepare future mothers of potential NAS-affected babies. This study will be the first to adapt an existing mobile NAS tool and develop an intervention for use with high-risk pregnant women and may be the first NAS-related intervention strategy designed to be administered to pregnant women in an OAT setting. Second, if effective, the mobile nature of our new tool will be readily scalable and well suited to tailoring for other populations of high-risk women (ie, with alcohol and or SUDs) of reproductive age. Moreover, such a tool will also be easy to update and modify, as more evidence emerges for how best to treat NAS. Although the tool is still too new to evaluate its cost efficiency, this study will prepare this tool for future analysis in the context of a larger study.

### Strengths and Limitations

The scope of the project is unavoidably limited. First, the relatively small number of sites and pregnant women participating in stage 3 hinders generalizability and the ability to determine effectiveness. However, this novel and critically relevant trial capitalizes on existing investments to allow us to gather data on efficacy and inform a fully powered randomized controlled trial. Second, recruitment below expectation and attrition are always possible. If recruitment becomes difficult, we will hold problem-solving meetings with program staff and research team on recruitment and study advertisement strategies. However, given our proposed study sample of n=30, we foresee no issue with obtaining our target enrollment across the 2 recruitment sites. Third, although attrition can be high in high-risk populations, our participants will already be embedded within the OAT system and, therefore, already engaged with services.

All activities outlined in the proposed application to develop and evaluate the mobile NAS caregiving intervention are accompanied with enhancing and evaluating the contextual fit (eg, acceptability and appropriateness) of the NAS caregiving intervention to support the application and scalability of this tool. This new tool will be designed to remain flexible to novel scientific breakthroughs in this domain such that new and modified modules can be easily created and integrated into this unique educational platform.

## Appendix

Multimedia Appendix 1 Grant review summary statement from the NIH.

## Abbreviations

CSQ-8: 8-item Client Satisfaction Questionnaire
ESC: Eat, Sleep, and Console
MPAS: Maternal Postpartum Attachment Scale
NAS: neonatal abstinence syndrome
NICU: neonatal intensive care unit
OAT: opioid agonist therapy
OUD: opioid use disorder
SUD: substance use disorder
SUS: Systems Usability Scale
TAU: treatment as usual
